**Methods/Design:**

Participants are men and women aged 18 to 70 years, at least 6 months post an ischemic or haemorrhagic stroke resulting in persisting language impairment (i.e., chronic aphasia); 220 patients will be screened for participation, with the goal of including at least 126 patients during the 26-month recruitment period. Basic language production and comprehension abilities need to be preserved (as assessed by the Aachen Aphasia Test).

Therapy consists of language-systematic and communicative-pragmatic exercises for at least 2 hours/day and at least 10 hours/week, plus at least 1 hour self-administered training per day, for at least three weeks. Contents of therapy are adapted to patients’ individual impairment profiles.

Prior to and immediately following the therapy/waiting period, patients’ individual language abilities are assessed via primary and secondary outcome measures. The primary (blinded) outcome measure is the A-scale (informational content, or 'understandability’, of the message) of the Amsterdam-Nijmegen Everyday Language Test (ANELT), a standardized measure of functional communication ability. Secondary (unblinded) outcome measures are language-systematic and communicative-pragmatic language screenings and questionnaires assessing life quality as viewed by the patient as well as a relative.

The primary analysis tests for differences between the therapy group and an untreated (waiting list) control group with respect to pre- versus post 3-week-therapy (or waiting period, respectively) scores on the ANELT A-scale. Statistical between-group comparisons of primary and secondary outcome measures will be conducted in intention-to-treat analyses.

Long-term stability of treatment effects will be assessed six months post intensive SLT (primary and secondary endpoints).

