### Objective

This prospective randomized controlled endpoint-blinded trial aims to examine whether, in chronic aphasia, the integrative approach to intensive language and communication therapy translates into functional improvements of everyday communication as well as improved health-related quality of life.

The principal research question is two-fold: (i) how effective is intensive integrative (i.e. combined language-systematic and communicative-pragmatic) language therapy, as currently administered in German in- and outpatient aphasia rehabilitation facilities, in improving everyday communication in post-acute/chronic post-stroke aphasia; and (ii) to what degree are these improvements maintained over a period of 6 months?

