### Power calculation

Sample size calculation was conducted for the comparison of mean change in ANELT A-scale score from t1 (baseline) to t2 (after 3 weeks of therapy or waiting) between the intensive language therapy group and the waiting list group (Figure 1). As a minimum difference of 8 points on the ANELT A-scale is considered clinically significant [32], group sample sizes of 63 were specified for each group in order to achieve 90% power to detect a difference of 10 points in the improvement of the mean ANELT A-scale score between the intensive treatment group after 3 weeks of intensive therapy and the waiting list group (difference of 1 point after 3 weeks of waiting), assuming a standard deviation for the difference in the ANELT A-scale score between t2 and t1 of 14 (10 for the waiting list group; Figure 1). Sample size was calculated for a two-sided Mann-Whitney test with significance level (alpha) of *P* <0.05. Assuming a patient non-participation rate of 25% prior to official study inclusion by randomization (for example due to the presence of exclusion criteria or no therapy funding by the respective sickness fund), 2 × 84 = 168 patients have to be recruited. The assumption of non-parametrical testing is rather conservative and the actual power will be larger if parametrical testing is possible.

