#### *Primary analysis*

The primary endpoint will be evaluated at baseline (t1) and immediately after 3 weeks of intensive therapy/waiting period (t2), by a statistical between-group comparison of the ANELT A-scale (ANCOVA) in an ITT design and with methods of multiple imputation taken into account. We expect that monotone missing data patterns will be observed (as described in [33]) and techniques appropriate for this situation will be applied. As a sensitivity analysis, the last-observation-carried-forward method will be applied.

Based on prior studies, we expect a therapy-induced improvement on the ANELT A-scale of M = 10 points (SD = 14) from baseline to immediately after 3 weeks of intensive therapy in the intensively treated group. For the waiting list group, we expect a change of M = 1 point (SD = 10) from baseline (t1) to the end of the 3-week waiting period (t2).

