#### *Secondary analyses*

Performance on the ANELT A-scale will also be evaluated at baseline (t1) and immediately after 3 weeks of intensive therapy/waiting period (t2), by a statistical between-group comparison of the ANELT A-scale (ANCOVA) in a treated-per-protocol design. In patients who are granted an extension beyond 5 weeks of intensive language therapy by their respective sickness fund, performance on the ANELT A-scale from pre to post therapy will again be evaluated immediately after the total intensive therapy period (i.e., 5–7 weeks after the baseline assessment = t2b), by a statistical between-group comparison of the ANELT A-scale (ANCOVA) in an ITT design where the last observation will be carried forward. This design feature is required due to the current heterogeneous therapy funding practices by the sickness funds. Initial funding is generally granted for 3 weeks, and for some patients (about 20%) extended for up to 7 weeks. The decision about the extension is made *after* rehabilitation therapy has started. Therefore, total duration of therapy cannot be planned *a priori*. Secondary endpoints (language-systematic and communicative-pragmatic screening measures; German version of the SAQOL-39, German Version of the CETI, ANELT B-scale as well as syntactic and non-verbal communication ratings) will be analysed in analogy to the primary analysis at baseline (t1) and immediately after 3 weeks of intensive therapy/waiting period (t2), by a statistical between-group comparison (ANCOVA) in an ITT design. Where applicable, the secondary endpoints will again be evaluated after a variable therapy extension for up to 7 weeks total therapy (t2b) in a subgroup of patients (cf. secondary analysis of the ANELT A-scale). Maintenance of therapy gains will be evaluated 6 months after termination of the first 3 weeks of intensive therapy (t4, long-term outcome) by statistical comparisons with t1, respectively. The amount of outpatient therapy provided between t2/t2b and t4 will be statistically controlled by covariate analyses.

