#### *Waiting list control group*

In analogy to the experimental group, therapy effects will be analysed immediately after 3 weeks of intensive therapy (t3). We expect a mean change of M = 10 after intensive therapy (comparisons of t1 and t3). We expect that therapy effects will be comparable to those of the experimental group. Outcome data of the waiting list group thus also serve to replicate the effect of intensive language therapy under routine clinical conditions. For control group patients who are granted more than 3 weeks of intensive language therapy, performance on the ANELT A-scale will again be evaluated immediately after the total period of therapy (i.e., 5–7 weeks of therapy, depending on the extension granted = t3b) in analogy to the experimental group. Again, we expect therapy effects to be comparable to those of the experimental group after 5–7 weeks of therapy. Maintenance of therapy gains will be evaluated 6 months after termination of the first 3 weeks of intensive therapy (t4, long-term outcome) by statistical comparisons with t1, respectively.

Taking into account that age, gender, time after stroke onset, aphasia type (fluent, non-fluent), aphasia severity (based on the AAT profile score), the total hours of therapy provided, type of stroke (cortical strokes with or without subcortical involvement), the amount of therapy-concomitant self-administered language practice (e.g. computer-aided practice), and medication and physio- and neuropsychological therapies might influence functional outcome, these factors will be included in a multivariate analysis with variable selection. No adjustment for multiplicity of testing will be provided. All analyses except for the primary analysis of the primary endpoint thus will not be strictly confirmatory.

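### Maintenance, the second half of the principal question, is evaluated only as t4 against t1, which shows whether a net gain over baseline remains and not how much of the end-of-therapy gain is kept

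*Protocol article*

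**What the plan says.** The Objective section of the protocol article states that "The principal research question is two-fold". Its second part asks "to what degree are these improvements maintained over a period of 6 months".

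The Secondary analyses section answers that part with a single comparison, made six months after the end "of the first 3 weeks of intensive therapy (t4, long-term outcome) by statistical comparisons with t1, respectively". The section on the waiting list control group repeats this wording for that group. Neither section names a contrast between t4 and the end of therapy (t2 or t3), a retained share, or a tolerable loss. The one addition is covariate control for outpatient therapy given between t2/t2b and t4.

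The abstract describes the timing differently: "Long-term stability of treatment effects will be assessed six months post intensive SLT". About 20% of patients may have therapy extended, to a total of up to 7 weeks, while t4 stays timed from the end of the first 3 weeks.

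The section on the waiting list control group also says that nothing apart from the primary analysis of the primary endpoint is strictly confirmatory.

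**The concern.** The improvement whose maintenance is in question arises between the start and the end of therapy. How far it is maintained depends on what happens between the end of therapy and t4. A comparison of t4 with t1 adds the gain and the later loss together and tests whether the sum differs from zero. A gain that is fully kept and a gain that is half lost can both give a significant result, so the test does not tell them apart.

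In the waiting-list group there is a second, smaller problem. Here t1 precedes the waiting period, and t2 is the score immediately before therapy. The t4-t1 change therefore includes any change during waiting.

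At stake is the answer to half of the principal question. A significant t4-t1 difference could be reported as maintained benefit when a large part of the gain has gone.

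**Working it through.** **Inputs from the protocol article**
- Expected gain in the therapy group, t1 to t2: an "improvement on the ANELT A-scale of M = 10 points (SD = 14) from baseline to immediately after 3 weeks" of therapy (Primary analysis).
- Expected change in the waiting-list group, t1 to t2: 1 point, SD 10 (Primary analysis). Expected change t1 to t3 in that group: 10 points (Waiting list control group).
- Clinical threshold (Power calculation): "As a minimum difference of 8 points on the ANELT A-scale is considered clinically significant".
- 63 patients per group, two-sided alpha 0.05 (Power calculation).

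**Assumptions, because the document gives no figure**
- SD of the t4-t1 change: 14, as for t2-t1, with a range of 10 to 20.
- No loss to follow-up before t4.
- Six months taken as 26 weeks.

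**The plan's own figure.** No sample size or power is stated for t4, so there is nothing to reproduce for this analysis. The figure of 63 per group belongs to the t1-t2 comparison and is used here only as the number available.

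**Step 1: chance of a significant t4-t1 result when half the gain is lost.** The true residual is 10 - 5 = 5 points. For a paired t-test, SE = SD/√n and the noncentrality is 5/SE.
- SD 14: SE = 14/√63 = 1.764; noncentrality 5/1.764 = 2.83; power 80%.
- SD 10: SE = 10/√63 = 1.260; noncentrality 3.97; power 97%.
- SD 20: SE = 20/√63 = 2.520; noncentrality 1.98; power 50%.
- With 50 instead of 63 patients at t4 and SD 14: 70%.

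**Step 2: smallest observed t4-t1 gain that is significant.** At SD 14 and n = 63 this is 2.00 × 1.764 = 3.5 points. That is 35% of the expected 10 points, a loss of about 65%, and below the 8-point threshold.

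**Step 3: what a direct contrast would give.** The SD of t4-t2 (or t4-t3) is also not stated. With n = 63, the 95% interval has a half-width of 2.5 points at SD 10 and 3.5 points at SD 14. A 5-point loss would be detected with 97% and 80% power respectively. The question can therefore be answered with usable precision at the planned size.

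**Step 4: waiting-list group.** Take the protocol's expected values (t2-t1 = 1, t3-t1 = 10) and a t4-t1 change of 5.
- Measured from t1, the retained share is 5/10 = 50%.
- Measured from the pre-therapy score t2, it is (5 - 1)/(10 - 1) = 4/9 = 44%.

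The effect of the reference point is real but small.

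**Step 5: interval to t4 in extended patients.** The extra test point applies to total therapy of 5 to 7 weeks, which is 2 to 4 weeks beyond the first 3. The interval from end of therapy to t4 is then 26 - 2 = 24 to 26 - 4 = 22 weeks.

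**The case against.** The strongest reply is that the loss can be read from planned results. In the same patients, (t2-t1) minus (t4-t1) is the mean loss, and t3 serves likewise in the waiting-list group. This stands for the point estimate. It does not give a confidence interval, because that depends on the correlation of the two changes, and no such comparison is planned. So it would go too far to say that the planned data cannot show decline; what is missing is an explicit contrast with its uncertainty.

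A second reply is that this is a condensed article and a separate analysis plan may hold more. That would excuse silence. Here the article itself fixes the comparison, in two places, and the one it fixes does not match the question.

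A third reply is that the analysis is exploratory. This stands and limits the consequence. A reader might infer that maintenance would be declared after half the gain is lost. The documents do not support that, because they state no rule for declaring it. The 80% is a probability of significance under an assumed SD.

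Two further readings are tempting. Pooling both groups (n = 126) would raise the probability to 98% at SD 14, but the plan describes maintenance separately by group and mentions no pooling. It might also seem that t4 comes only about five months after therapy in all extended patients; the shortfall is 2 to 4 weeks, and the main text defines t4 clearly, while the abstract only abbreviates.

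Finally, both arms are treated by t4, so a t4-t2 or t4-t3 contrast is as uncontrolled as t4-t1. That is correct: the change aligns the analysis with the question but does not make it a randomised comparison.

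**Conclusion.** The point holds as an error in the choice of a secondary analysis. The protocol asks to what degree gains are kept and names only a comparison that shows whether some net gain remains. With 63 patients per group, no attrition and an assumed SD of 14, that comparison would be significant with about 80% probability after loss of half the expected gain. The figure runs from 97% to 50% over assumed SDs of 10 to 20 and falls with attrition. The waiting-list reference point adds an expected 1 point to t4-t1 in that group.

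The confirmatory test of t1 to t2 is not affected. The risk is a misleading secondary conclusion on half of the principal question, and the change should be made for that reason.

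**What to change.** In both sections, define the maintenance estimate as the within-patient change from the end of the 3-week therapy to t4: t4-t2 in the experimental group and t4-t3 in the waiting-list group. Report it with a 95% confidence interval and the retained share of the gain. Keep t4 against the pre-therapy score (t1 experimental, t2 waiting list) as a description of net gain.

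For patients with extended therapy, keep the common 3-week reference in the main estimate, so that the reference does not depend on a funding decision taken after therapy starts. Because their t4 score also reflects the extra weeks of therapy, add t4 against t2b/t3b as a supplementary description. Report the actual interval from end of therapy to t4 (about 22 to 24 weeks) and align the abstract's wording with it.

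A formal retention margin is not needed. At SD 14, n = 63 and no true loss, the chance that the lower limit clears a 4-point margin is only Φ(4/1.764 - 1.96) = 62%, and for 2 points about 20%. An estimate with its interval is the sounder aim.

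The cost is analysis wording and slightly more analysis work, with no new visits or data. The retention estimate may look less favourable than the t4-t1 result.

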#### *Waiting list control group*

In analogy to the experimental group, therapy effects will be analysed immediately after 3 weeks of intensive therapy (t3). We expect a mean change of M = 10 after intensive therapy (comparisons of t1 and t3). We expect that therapy effects will be comparable to those of the experimental group. Outcome data of the waiting list group thus also serve to replicate the effect of intensive language therapy under routine clinical conditions. For control group patients who are granted more than 3 weeks of intensive language therapy, performance on the ANELT A-scale will again be evaluated immediately after the total period of therapy (i.e., 5–7 weeks of therapy, depending on the extension granted = t3b) in analogy to the experimental group. Again, we expect therapy effects to be comparable to those of the experimental group after 5–7 weeks of therapy. Maintenance of therapy gains will be evaluated 6 months after termination of the first 3 weeks of intensive therapy (t4, long-term outcome) by statistical comparisons with t1, respectively.

Taking into account that age, gender, time after stroke onset, aphasia type (fluent, non-fluent), aphasia severity (based on the AAT profile score), the total hours of therapy provided, type of stroke (cortical strokes with or without subcortical involvement), the amount of therapy-concomitant self-administered language practice (e.g. computer-aided practice), and medication and physio- and neuropsychological therapies might influence functional outcome, these factors will be included in a multivariate analysis with variable selection. No adjustment for multiplicity of testing will be provided. All analyses except for the primary analysis of the primary endpoint thus will not be strictly confirmatory.

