### Study design

The study design is depicted in Figure 1. The inclusion of a waiting list control group, intended to control unspecific effects of language therapy, circumvents the ethical dilemma of withholding potentially efficacious treatment from patients. After a 3-week waiting period, the control group receives the same treatment as the experimental group.

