### Outcome measures

#### *Primary endpoint*

Mean difference on the ANELT [28] A-scale (understandability), operationalized as the difference in scores between the test point immediately after the 3-week intensive therapy (or waiting) period, and the test point immediately prior to the initiation of treatment (i.e., the difference of the scores, i.e., 't2’ minus those at test point 't1’; Figure 1). The ANELT tests verbal communicative ability in everyday communicative situations, shows a high concurrent validity with other standard linguistic assessment tools and is particularly suitable in the post-acute/chronic phase after stroke.

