### Statistical analyses

Analyses of primary and secondary endpoints will be performed in the (intention-to-treat) ITT population consisting of all randomized patients who received at least one day of therapy, or were at least one day on the waiting list. If data are normally distributed, parametrical methods will be used. The primary analysis will test for differences between the therapy group and the untreated (waiting list) control group with respect to the mean change (relative to baseline performance at the test point prior to the instantiation of therapy) on the ANELT A-scale at the test point immediately following the 3-week intensive therapy (or respective waiting) period. As opposed to the comparison group, which is not expected to demonstrate a clinically significant change between the two baseline assessments prior to SLT on the ANELT A-scale scores, the therapy group on average is expected to show a clinically significant improvement between the two test points. In the following paragraphs, statistical analyses are explained in more detail.

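### The waiting-list group's therapy effect is measured from t1 to t3, which includes the untreated wait; its therapy interval is t2 to t3

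*Protocol article*

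**What the plan says.** Under Study design, the article says of the control arm: "After a 3-week waiting period, the control group receives the same treatment as the experimental group". Under Primary analysis it gives the expected changes between t1 and t2. For the treated arm, "we expect a therapy-induced improvement on the ANELT A-scale of M = 10 points (SD = 14) from baseline" to the end of three weeks of therapy. For the waiting-list arm, "we expect a change of M = 1 point (SD = 10) from baseline (t1) to the end" of the wait.

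The section Waiting list control group then describes how this arm is analysed after its own therapy, at t3. It presents the analysis as parallel to that of the experimental group, and states: "We expect a mean change of M = 10 after intensive therapy (comparisons of t1 and t3"). It adds: "We expect that therapy effects will be comparable to those of the experimental group", and says that these data also serve as a replication of the therapy effect. For patients with extended funding, a further assessment at t3b is to be handled in the same way.

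Two other places bear on the reference score. Primary endpoint names as the starting value "the test point immediately prior to the initiation of treatment" and then writes the endpoint as t2 minus t1. Statistical analyses expects no clinically significant change in the comparison group "between the two baseline assessments prior to SLT on the ANELT A-scale scores", so it treats both t1 and t2 as pre-therapy scores in that group.

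**The concern.** In the experimental group, t1 is the last score before therapy and t2 the first score after three weeks of it. In the waiting-list group, the last score before therapy is t2. Measuring that group's therapy effect from t1 adds the untreated wait and one more test administration to the interval. The two contrasts then differ in length and content, although the plan presents them as parallel.

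What is at stake is the replication claim. Once the waiting-list group has been treated, no untreated group remains, so the analysis is a within-group change. The wait is the only information that separates therapy from retest effects, regression to the mean and time in these patients. A t1-to-t3 contrast does not use it and counts that change as therapy gain.

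The expected value is also unclear. A reader cannot tell whether 10 points is the gain from therapy or the total over wait and therapy.

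**Working it through.** **Inputs, all from the protocol article**
- Waiting-list group, t1 to t2 (wait): mean 1, SD 10 (Primary analysis).
- Experimental group, t1 to t2 (therapy): mean 10, SD 14 (Primary analysis).
- Waiting-list group, t1 to t3: mean 10, no SD given (Waiting list control group).
- 63 patients per group (Power calculation).

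**The intervals side by side**
- Experimental, t1 to t2: 3 weeks of therapy; ANELT administrations 1 and 2.
- Waiting list, t1 to t3: 3 weeks of waiting plus 3 weeks of therapy; ANELT administrations 1, 2 and 3.
- Waiting list, t2 to t3: 3 weeks of therapy; ANELT administrations 2 and 3.

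**Identity**

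(t3 − t1) = (t2 − t1) + (t3 − t2)

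The t1-to-t3 change therefore exceeds the change over the therapy interval by exactly the waiting change, whatever that turns out to be.

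**Can the stated 10 points be reproduced?**
- Reading A: therapy adds 10 points on top of the waiting change. Then t1 to t3 = 1 + 10 = 11. The stated 10 is not reproduced.
- Reading B: the experimental group's 10 points already contain a one-off non-specific change of 1, so the therapy part is 10 − 1 = 9. Then t1 to t3 = 1 + 9 = 10. The stated 10 is reproduced.

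The article does not say which reading it intends. Taken as written, 1 point for t1 to t2 and 10 points for t1 to t3 imply 10 − 1 = 9 points for t2 to t3.

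**Size on the plan's expectations**

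The wait contributes 1 point. That is 1/10 = 10% of the t1-to-t3 change under reading B and 1/11 = 9% under reading A.

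**Precision, for scale**
- Mean t2-to-t3 change, assuming the experimental group's SD of 14 also applies here: SE = 14/√63 = 1.76.
- Mean t1-to-t3 change: SD = √(14² + 10² + 2·ρ·14·10), where ρ is the correlation between the two period changes. The article does not give ρ. For assumed values from −0.5 to 0.25, the SD runs from 12.5 to 19.1 and the SE from 1.57 to 2.41.

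The expected 1-point difference is smaller than one standard error. It is also well below the 8 points that Power calculation treats as clinically significant.

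**The case against.** The strongest reply has four parts.

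First, there is no numerical contradiction. The 1 point and the 10 points refer to different intervals, and the article promises only comparable effects in the two groups; 9 against 10 is comparable. This stands. A reader might infer from the two figures that the plan's expectations clash and that 11 is the only correct total. That holds only if all 10 experimental points are specific to therapy and add to the waiting change. The word the article uses for that improvement allows this reading, but the article does not settle it.

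Second, t3 minus t2 is not a perfect counterpart either. It compares a second with a third ANELT administration, whereas the experimental contrast compares a first with a second. If retest or regression effects arise mainly at the first retest, the experimental contrast contains them and t3 minus t2 largely does not. This stands as a caveat. It does not justify leaving three untreated weeks inside a therapy effect.

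Third, t1 is a common reference, since the six-month assessment is compared with t1 in both groups, and alternating the two parallel ANELT versions already limits practice effects. A common starting point suits a long-term total change, but it does not make t1 the pre-therapy score of patients who begin therapy after t2. Alternation does not remove the wait. If it is strict, t1 and t3 would even use the same version, while the experimental t1 and t2 use different ones.

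Fourth, the wording under Primary endpoint defines the primary endpoint as t2 minus t1 and does not bind the later waiting-list analysis. That is correct. The point rests mainly on the sequence of wait and therapy in this group, which the article states plainly.

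**Conclusion.** The point holds as a flaw in the choice of contrast. The waiting-list group's t1-to-t3 change mixes waiting with therapy, is not the counterpart of the experimental group's t1-to-t2 change, and passes any waiting change into the replicated effect. On the plan's expectations the amount is 1 point out of 10 or 11. The actual amount will be whatever change occurs during the wait. The expected value needs one clarifying sentence, because the article leaves open whether therapy is meant to add 9 or 10 points.

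A reader might go further and infer that the main result is at risk. The documents do not support that. The primary analysis compares the groups over t1 to t2, and the sample size rests on the same interval; neither uses t3. The article also declares every analysis other than the primary one not strictly confirmatory. Nor does it give any basis for a waiting change larger than 1 point. The correction is worth making, but it is not essential to the validity of the trial.

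The conclusion assumes that t1, t2 and t3 are as the text describes them; the design figure is not available.

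**What to change.** In Waiting list control group:
- Define this group's therapy effect as t3 minus t2, and as t3b minus t2 for patients with extended therapy.
- State the expected change for t2 to t3 so that it agrees with Primary analysis. It is 9 if 10 is the total from t1, or 10 if therapy itself is meant to add 10, in which case the t1-to-t3 expectation becomes 11.
- Label any t3-minus-t1 result as total change including the wait.
- Note that t3 minus t2 compares the second with the third ANELT administration, so first-retest effects may differ from those in the experimental group's t2 minus t1.

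The cost is a change of wording. The t2 assessment is already scheduled for all patients, so no new data are needed. Patients whose t2 score is missing would need handling in this contrast, and the plan already provides for imputation of missing scores in the primary analysis.

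### The waiting-list therapy effect is expected to be comparable to the experimental arm's and is used as a replication, but the only contrast named for it is a within-group change from t1 to t3, which cannot show comparability

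*Protocol article*

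**What the plan says.** All of this is in the protocol article.

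- **Waiting list control group, contrast named.** Therapy effects at t3 are to be analysed by analogy with the experimental group, and the expectation is "We expect a mean change of M = 10 after intensive therapy (comparisons of t1 and t3").
- **Waiting list control group, comparability.** "We expect that therapy effects will be comparable to those of the experimental group". For patients with extended therapy: "Again, we expect therapy effects to be comparable to those of the experimental group after 5–7 weeks of therapy".
- **Waiting list control group, use of the data.** "Outcome data of the waiting list group thus also serve to replicate the effect of intensive language therapy under routine clinical conditions".
- **Waiting list control group, status.** No multiplicity adjustment is made, and everything except the primary analysis of the primary endpoint is declared not strictly confirmatory.
- **Primary analysis.** For the experimental arm, "we expect a therapy-induced improvement on the ANELT A-scale of M = 10 points (SD = 14) from baseline to immediately after 3 weeks" of therapy. For the waiting-list arm, "we expect a change of M = 1 point (SD = 10) from baseline (t1) to the end of the 3-week waiting period (t2").
- **Power calculation.** "group sample sizes of 63 were specified for each group in order to achieve 90% power". On the size of effect that matters: "As a minimum difference of 8 points on the ANELT A-scale is considered clinically significant".
- **Secondary analyses.** The between-group ANCOVAs with a stated time point are at t2 or t2b. About 20% of patients are expected to receive extended therapy.

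**The concern.** Comparability of two therapy effects is a statement about the difference between them. The named contrast concerns one arm only and asks whether its change differs from zero. A significant result shows that scores rose. It does not show that they rose by about as much as in the experimental arm.

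The time windows do not match either. The experimental arm's gain runs from t1 to t2, a period of therapy only. The waiting-list contrast runs from t1 to t3, which is three weeks of waiting followed by three weeks of therapy. Any change during the wait is counted as therapy effect.

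At stake is how the trial's only internal replication is reported. If a significant t1–t3 change were taken as support for comparability, a gain half as large as expected would often pass. The primary result and the sample size are not affected.

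**Working it through.** **Inputs**
- 63 per arm, two-sided alpha 0.05 (Power calculation).
- SD of change 14 under therapy, 10 while waiting (Power calculation; Primary analysis).
- Expected changes: 10 points under therapy and 1 while waiting (Primary analysis); 10 from t1 to t3 in the waiting-list arm (Waiting list control group).
- About 20% with extended therapy (Secondary analyses).
- *Assumption:* no SD is given for the waiting-list t1–t3 or t2–t3 change. I take 14 and vary it. I also assume complete data and normal changes.

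The protocol gives no power or precision for this analysis, so there is no figure to reproduce. I use 63 as the planned number.

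**1. The windows differ.** On the plan's own expectations, a t1–t3 change of 10 that includes 1 point during the wait leaves 10 − 1 = 9 points for the therapy period, against 10 in the experimental arm. The gap is small, but the two quantities are not the same.

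**2. What the within-group test can distinguish.** One-sample t-test on the change, 62 df, critical t = 2.00:
- SE = 14/√63 = 1.76. The smallest significant mean change is 2.00 × 1.76 ≈ 3.5 points, less than half of the plan's 8-point threshold.
- At a true change of 5, the noncentrality is 5/1.76 = 2.83 and the power is 80% (Wilcoxon signed-rank, simulated: 78%).
- At a true change of 10, the power exceeds 99%.

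Dependence of the 5-point figure on the assumptions:

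| n | SD | Power at a true change of 5 |
|---|---|---|
| 63 | 10 | 97% |
| 63 | 12 | 90% |
| 63 | 14 | 80% |
| 63 | 17.2 | 62% |
| 63 | 20 | 50% |
| 57 | 14 | 76% |
| 50 | 14 | 70% |

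**3. What a direct comparison would deliver.** Difference in therapy gains, experimental (t2 − t1) minus waiting list (t3 − t2), SD 14 in both:
- SE = 14 × √(2/63) = 2.49. The 95% half-width is 1.98 × 2.49 ≈ 4.9 points.
- A test of no difference would be non-significant 49% of the time at a true difference of 5, and 11% at 8. Absence of significance is therefore not evidence of comparability either; the interval is what informs.

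**4. Extended-therapy subgroup.** 20% of 63 = 12.6, so about 12–13 per arm:
- n = 13: SE = 14 × √(2/13) = 5.49; half-width 2.06 × 5.49 ≈ 11.3.
- n = 12: SE = 14 × √(2/12) = 5.72; half-width 2.07 × 5.72 ≈ 11.9.
- A true difference of 8 points would be non-significant 71–73% of the time.
- At SD 10 the half-width is still 8.1–8.5 points.

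**The case against.** **It is an expectation, not a decision rule.** This stands. A reader might infer that the trial will declare the effects comparable whenever the t1–t3 change is significant. The document says no such thing; it uses the same language of expectation elsewhere for anticipated results. The 80% is the chance of p < 0.05 at half the expected gain, not the chance that the trial would call 5 points comparable to 10. An observed gain of 5 would also be visible as half of the stated 10.

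**Replication is weaker than equivalence, and the analyses are labelled non-confirmatory.** Also fair. Replication can be read as patients improving again after therapy, which a pre-post change can address, though without a control. That reading does not cover the comparability statements, and the label does not make a test against zero answer a question about a difference.

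**The analogy with the experimental group may imply a between-group ANCOVA, and a fuller document may specify it.** Possible. But no untreated group remains at t3, and no comparator is named for t3 or t3b. The point concerns the mismatch between the contrast that is named and the use made of it, not the absence of detail.

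**The SD is assumed.** Correct. SD 14 is stated only for the experimental arm from t1 to t2, and at SD 20 the 80% falls to 50%.

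**A formal equivalence margin would be arbitrary.** Accepted. The 8-point figure is a threshold for clinical significance, not an equivalence margin, and it is close to the whole expected net effect of 10 − 1 = 9. Requiring the 95% CI to lie within ±8 would still pass a true 5-point difference about 22% of the time at SD 14.

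**Conclusion.** The point holds as a mismatch between the named contrast and the inference drawn from it. The t1–t3 change in the waiting-list arm tests against zero and includes the wait, so it cannot support comparability. With 63 patients and SD 14 it is significant about 80% of the time at half the expected gain; across SDs of 10 to 20 the range is 97% to 50%. A direct comparison on the same data would locate the difference to within about ±4.9 points at SD 14. In the 5–7-week subgroup it would be about ±11 to ±12 points, too wide to support a comparability statement.

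The effect is limited to the wording of a non-confirmatory replication. The documents do not support reading this as a flaw in the primary analysis or as a commitment to report equivalence.

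**What to change.** In the section on the waiting-list control group:

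1. Add the difference between the arms' 3-week therapy gains on the ANELT A-scale (experimental t2 minus t1; waiting list t3 minus t2) with a 95% CI.
2. Base any statement on comparability on that interval, not on a significant within-group change or a non-significant between-arm test.
3. Describe the t1–t3 change as an uncontrolled pre-post change.
4. For the 5–7-week subgroup, report the estimate and CI as descriptive only.

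No formal ±8-point equivalence rule is needed. The cost is one extra exploratory contrast on scores already planned, and a more cautious replication statement; no added patients or visits.
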